## Abstract

**Background:**

Positive end-expiratory pressure (PEEP) at minimum respiratory elastance during mechanical ventilation (MV) in patients with acute respiratory distress syndrome (ARDS) may improve patient care and outcome. The Clinical utilisation of respiratory elastance (CURE) trial is a two-arm, randomised controlled trial (RCT) investigating the performance of PEEP selected at an objective, model-based minimal respiratory system elastance in patients with ARDS.

**Methods and design:**

The CURE RCT compares two groups of patients requiring invasive MV with a partial pressure of arterial oxygen/fraction of inspired oxygen (PaO2/FiO2) ratio ≤ 200; one criterion of the Berlin consensus definition of moderate (≤ 200) or severe (≤ 100) ARDS. All patients are ventilated using pressure controlled (bi-level) ventilation with tidal volume = 6–8 ml/kg. Patients randomised to the control group will have PEEP selected per standard practice (SPV). Patients randomised to the intervention will have PEEP selected based on a minimal elastance using a model-based computerised method. The CURE RCT is a single-centre trial in the intensive care unit (ICU) of Christchurch hospital, New Zealand, with a target sample size of 320 patients over a maximum of 3 years. The primary outcome is the area under the curve (AUC) ratio of arterial blood oxygenation to the fraction of inspired oxygen over time. Secondary outcomes include length of time of MV, ventilator-free days (VFD) up to 28 days, ICU and hospital length of stay, AUC of oxygen saturation (SpO_2_)/FiO_2_ during MV, number of desaturation events (SpO_2_ < 88%), changes in respiratory mechanics and chest x-ray index scores, rescue therapies (prone positioning, nitric oxide use, extracorporeal membrane oxygenation) and hospital and 90-day mortality.

**Discussion:**

The CURE RCT is the first trial comparing significant clinical outcomes in patients with ARDS in whom PEEP is selected at minimum elastance using an objective model-based method able to quantify and consider both inter-patient and intra-patient variability. CURE aims to demonstrate the hypothesized benefit of patient-specific PEEP and attest to the significance of real-time monitoring and decision-support for MV in the critical care environment.

**Trial registration:**

Australian New Zealand Clinical Trial Registry, ACTRN12614001069640. Registered on 22 September 2014.

(https://www.anzctr.org.au/Trial/Registration/TrialReview.aspx?id=366838&isReview=true) The CURE RCT clinical protocol and data usage has been granted by the New Zealand South Regional Ethics Committee (Reference number: 14/STH/132).

## Background

Mechanical ventilation (MV) support is crucial for patients with acute respiratory distress syndrome (ARDS). While there is agreement on the preference for lower tidal volumes [1, 2], there is relatively little consensus on the selection of positive end-expiratory pressure (PEEP) [3–9]. Traditionally, lower PEEP has been used [10, 11], but low PEEP can lead to increases in oxygen desaturation and hypoxaemia [4, 12] and worsening of lung injury, indicated by greater use of rescue therapies and deaths after rescue therapy [9]. High PEEP can increase alveolar recruitment, but can decrease cardiac output and lead to further lung injury due to barotrauma and/or volutrauma [13] or overdistension [4, 9].

PEEP can be optimised to reduce hypoxaemia [6] and intrapulmonary shunting [7] and improve gas exchange [8] and oxygenation [4, 14, 15], by maintaining recruitment of injured or collapsed alveoli [13]. In patients with ARDS, PEEP reduces ventilator-induced lung injury (VILI) [4, 9], increases recruitment [14–16], and reduces inflammatory mediators in plasma and bronchoalveolar lavage fluid [8]. MV strategies combining low tidal volumes with recruitment manoeuvres (RMs) and higher PEEP to prevent VILI have been hypothesized as ideal for lung protection [6, 17]. However, currently, there is still no standardized approach to the selection of this optimal PEEP, or to deciding how often PEEP should be adjusted or recalculated.

Reports from experimental animal trials performed by Carvalho et al., Suarez-Sipmann et al. and Lambermont et al. [18–20] indicate that pigs induced with ARDS experience minimal respiratory elastance at a specific PEEP associated with higher oxygenation, maximum recruitment, and higher functional residual capacity, all without signs of lung overdistension. Equally, it has been proposed that PEEP should be set whereby the lung has minimal respiratory elastance (or maximum compliance), which could be clinically beneficial by balancing the risks of PEEP that is set too low or too high [21–23]. Aside from the work by Suter et al. [21], Pintado et al. also showed that PEEP selection at minimal elastance is beneficial to patients [22]. Despite some consistent findings, the application of minimal elastance PEEP selection remains limited and hindered by the lack of an objective, reliable, and easy-to-use method to determine elastance at the bedside in real time.

[name] et al. showed the potential benefit of minimal-elastance PEEP selection in a pilot study [23, 24]. Following the study, a phase-2 randomised controlled trial (RCT) was designed to assess mechanical ventilation at minimal elastance PEEP in patients with ARDS versus standard practice of care in a single-centre hospital. In particular, patient-specific respiratory system elastance and corresponding minimal elastance PEEP is determined using a validated model-based method and computer software [25]. This trial uses real-time-identified patient-specific respiratory system elastance, and thus the trial is named the Clinical utilisation of respiratory elastance (CURE) RCT. This manuscript presents the detailed clinical protocol for the phase-2 CURE RCT. This trial is registered with the Australian New Zealand Clinical Trial Registry (ANZCTR): ACTRN12613001006730.

## Methods and trial design

### Study design and setting

The CURE RCT is a two-arm RCT comparing model-based mechanical ventilation (MBV) with current standard practice mechanical ventilation (SPV) in patients with a ratio of partial pressure of arterial blood oxygen (PaO2)/fraction of inspired oxygen (FiO2) (P/F ratio) ≤ 200. It is to be conducted in a single-centre hospital intensive care unit (ICU) at Christchurch Hospital in Christchurch, New Zealand.

The primary objective is to assess the impact of model-based ventilation in PEEP selection (MBV) therapy on clinically significant patient outcomes and patient-centred quality of care metrics. The other objectives of this study include (1) to provide the knowledge and methods to make care more patient-specific and timely to optimise treatment and improve outcomes in a large cohort of critically ill patients and (2) to improve the understanding of the pathophysiological basis of critical illness through what we learn about the hourly and daily evolution of lung injury in terms of patient-specific elastance and response to care through this study.

The primary outcome of this study is the area under the curve (AUC) of PaO2/FiO2 over the period of mechanical ventilation. Secondary outcomes include length of time of MV (LoMV), ventilator-free days (VFD) up to 28 days, ICU and hospital length of stay (LoS), AUC of SpO_2_ (oxygen saturation)/FiO_2_ during MV, number of desaturation events (frequency and fraction of time SpO_2_ < 88%), changes in respiratory mechanics and chest x-ray index scores, rescue therapies (prone positioning, nitric oxide use, extracorporeal membrane oxygenation (ECMO)) and hospital and 90-day mortality. These outcomes and their corresponding four levels of specification based on Zarin et al., 2011 is shown in Table 1. The secondary analysis includes comparison of the means of LoMV, VFD, hospital and ICU LoS, 90-day mortality, chest x-ray index scores and rescue therapies used.

**Table 1 Tab1:** Four levels of specification in primary and secondary outcomes

Level 1 Domain	Oxygenation		MV		Length of stay			Other	
Level 2 Specific domain	AUC P/F ratio	AUC Spo2/FiO2	Length of MV	Ventilator free days (VFD) up to 28 days	Hospital	ICU	90-Day mortality	Chest x-ray index scores	Rescue therapies
Level 3 Specific metric	Difference in AUC		Number of days	28 days – days of MV	Number of days		Time to event	Index scores over period of MV	Number of therapies used
Level 4 Method of aggregation	Comparisons of the of means of AUC		Comparisons of the means of number of days	Comparisons of the means of VFD	Comparisons of the means of length of stay		Comparison on number of 90-day mortality	Comparison of index scores over time	Comparison of rescue therapies used.

*P/F* partial pressure of arterial oxygen/fraction of inspired oxygen, *SPO*_*2*_ oxygen saturation, *MV* mechanical ventilation, *FiO*_*2*_ fraction of inspired oxygen

A difference in primary and secondary outcomes will show the impact of MBV compared to SPV. No difference would show that enhanced, model-based metrics of patient-specific condition have no effect on patient-centred or clinical outcomes. Either outcome will yield clinical guidance.

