### Two-arm RCT

Eligible patients are randomised to either the model-based intervention group (MBV) or the control group (SPV). Both groups will have designated computer software to monitor their breathing [25]. The software uses real-time measurements of pressure and flow from the ventilator to objectively calculate the patient-specific and breath-specific respiratory system elastance for every breath [25].

Participants on MBV will undergo recruitment manoeuvres (RM), an initial maximum recruitment manoeuvre (RM_Max_) or subsequent PEEP adjustment and monitoring procedure (PUMP) mini recruitment manoeuvres. The respiratory elastance at each PEEP step during these protocolised RMs is calculated and recorded. The software will recommend a patient-specific minimal-elastance PEEP to the clinicians in setting ventilator PEEP. Patients on SPV will have PEEP selected using current clinical practice without the aid of the software, but all breaths will be analysed and elastance recorded; clinical staff will be blinded to these data.

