### General procedures

#### Procedures for the control group (SPV)

The procedures are as follows:
PEEP is selected as per standard practice.The decision to carry out a staircase recruitment manoeuvre will be based on clinical judgement. The protocol for performing the staircase recruitment manoeuvre is explained in “Recruitment manoeuvres (RM)”.ABGs will be taken twice daily.Ventilator data are collected continuously until the ventilator is disconnected.

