### PUMP: PEEP adjustment and monitoring procedure

PUMP is a regular mini-recruitment manoeuvre procedure designed to adjust PEEP based on patient-specific changes in condition. This mini-RM is also guided by CURE software and moves between ±4 cmH_2_O from the current PEEP. PUMP should be performed twice daily during normal working hours (0800–1800 hours) or at any other time if lung de-recruitment is considered to be the likely cause of new desaturation. The Pi will be left the same as in the current ventilator settings. To ensure a PUMP can be safely carried out, the RM checklist and preparation steps are to be followed. If the checklist preconditions are met, the PUMP may be carried out.

The following instructions are given to the clinician:
Titrate sedation so the patient is not verbally responsive and has loss of their eyelash reflex. Use fentanyl or morphine increments with propofol to provide a “balanced” deeper sedation level. Give rocuronium 0.5–1.0 mg/kg through a reliable i.v. line; ensure the line is flushed.Set the ventilator to SIMV-PC mode with the appropriate aforementioned settings.Reduce the PEEP to 4 cmH_2_O less than the current PEEP setting. The CURE software cannot estimate an optimal PEEP that is lower than the current PEEP setting.Start PUMP on the CURE soft programme.Follow the steps of the CURE soft PUMP protocol. During the PUMP procedure, increase PEEP in two steps of 4 cmH_2_O. Then decrease PEEP in two steps of 4 cmH_2_O (you may need to adjust the FiO_2_ to keep the SpO_2_ ≥ 90%).Once you have returned PEEP to the starting PEEP level (initial PEEP − 4 cmH_2_O), perform a second PUMP using the same method described in point 5.The CURE soft programme will recommend a new PEEP at the end of the second PUMP. You may either accept this computerised recommendation, or reject it (with a reason) if you feel the new PEEP level is inappropriate. If rejected, record your reason(s) on the programme.Return the patient to the previous ventilation mode.Adjust to V_T_ ≤ 6–8 ml/kg IBW. If the plateau pressure is > 30 cmH_2_O, adjust the V_T_ down to 4–6 ml/kg IBW and tolerate permissive hypercapnia. Also ensure that the DP remains ≤15 cmH_2_O. You may increase the respiratory rate up to 30 breaths/min provided there is no significant auto-PEEP causing breath stacking.Reduce the ETT cuff pressure to the previous level and re-set ventilator alarms to previous settings.Take an ABG 30 to 60 mins following the conclusion of the procedure

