### Study outcome

The trial will utilise a primary composite end point incorporating the AUC of the P/F ratio over the period of MV. Every participant in the intervention (MBV) group is compared with every participant in the control (SPV) group. Test statistics will be calculated using the one-sided Wilcoxon rank sum test at alpha of 0.05. If results show no statistically significant difference between the intervention and control, it will result in the rejection of the intervention treatment as a standard of care and thus, the secondary clinical outcome assessments will include the number of desaturation events measured as peripheral capillary oxygen saturation < 90%, LoMV, VFD for 28 days, the quality of mechanical ventilation care measured as the AUC of SpO_2_/FiO_2_ and chest x-ray index scores over time. The test statistic will be calculated using the one-sided Wilcoxon rank sum test at alpha of 0.05.

A difference in the primary outcome will show the impact of MBV compared to SPV. No difference would show that enhanced, model-based metrics of the patient-specific condition have no effect on patient-centred or clinical outcomes. Either outcome will yield clinical guidance.

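### The trial compares a whole MBV strategy with usual care, so a null result cannot show, as the protocol says it would, that model-based metrics have no effect

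*Protocol article*

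**What the plan says.** The protocol article states its question in terms of PEEP choice. The abstract describes a trial "investigating the performance of PEEP selected at an objective, model-based minimal respiratory system elastance in patients with ARDS", and its Discussion paragraph says "CURE aims to demonstrate the hypothesized benefit of patient-specific PEEP". Under Study design and setting, "The primary objective is to assess the impact of model-based ventilation in PEEP selection (MBV) therapy on clinically significant patient outcomes".

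The treatment sections describe more than a PEEP choice. Under Two-arm RCT, "Participants on MBV will undergo recruitment manoeuvres (RM), an initial maximum recruitment manoeuvre", followed by PUMP procedures. The PUMP section adds "PUMP should be performed twice daily during normal working hours". For the control arm, "The decision to carry out a staircase recruitment manoeuvre will be based on clinical judgement".

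Two sentences say how results will be read. For a difference, under Study design and setting: "A difference in primary and secondary outcomes will show the impact of MBV compared to SPV". For no difference, under Study outcome: "No difference would show that enhanced, model-based metrics of the patient-specific condition have no effect on patient-centred or clinical outcomes". Each sentence appears in nearly the same words in the other of these two sections.

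**The concern.** The null sentence credits a null result to one component, the elastance metric, although randomisation separates the arms on several components at once. If the manoeuvres, or the sedation and muscle relaxant that accompany them, act on the outcomes in their own right, the comparison contains their effect too. A benefit of elastance-guided PEEP could be masked by a cost of the rest of the package, and the printed rule would then declare the metric ineffective.

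What is at stake is the published conclusion. The protocol says that either result will give clinical guidance, and Study outcome adds that a non-significant result leads to rejection of the intervention as a standard of care. Declining to adopt a strategy whose benefit was not demonstrated is a defensible decision about the strategy. Declaring that model-based metrics have no effect is a scientific claim about a component that the trial does not isolate.

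**Working it through.** The protocol gives no figure for this point, so the check is a comparison of its sections.

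**1. What differs between the arms by plan**

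| Element | MBV | SPV |
|---|---|---|
| Initial maximum manoeuvre | Yes, carried out twice (RM_Max section) | None |
| PUMP | Twice daily, two cycles per session (PUMP section), up to 10 days (Duration of the intervention) | None; both procedures are reserved for MBV (Recruitment manoeuvres) |
| Staircase manoeuvre (SRM) | Not part of the arm | Discretionary; may be considered at PEEP ≥ 15 cmH2O with FiO2 ≥ 60% (Standard practice SRM) |
| Deep sedation and rocuronium for manoeuvres | In the instructions for every RM_Max and PUMP | In the instructions for an SRM, if one is done |
| How PEEP is set | Software recommendation, which the clinician may accept or reject | Clinical judgement |

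The intervention-group procedures call for paralysis only if required, while the RM_Max and PUMP instructions list it as a step. The point does not depend on which wording governs.

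**2. Scheduled exposure**

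- PUMP sessions: 2 per day × 10 days = 20 at most.
- PEEP staircases in MBV: 2 (RM_Max) + 20 × 2 cycles = 42 at most.
- Scheduled in SPV: 0.

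The MBV figure is a ceiling, because PUMPs stop on weaning criteria or at the clinician's discretion. The SPV figure is a floor, because an SRM may be done.

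**3. Does the protocol treat the manoeuvres as active?** Yes, in three places.

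- Consent procedure describes the recruitment techniques in both arms as used to improve oxygenation and ventilation mechanics.
- The RM_Max instructions say that the first of the two manoeuvres serves to recruit collapsed lung, and only the second to estimate PEEP.
- Repeating the RM_Max lists, among its conditions, a PUMP that failed to improve oxygenation, so a PUMP is expected to be able to improve it.

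The primary outcome is itself oxygenation (AUC of P/F). Sedation also bears on duration of ventilation: Weaning assessment looks for falling sedation requirements before the move to assisted spontaneous breathing.

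**4. What a null can mean.** Suppose that effects on length of ventilation multiply. Take the 25% reduction from the sample size section as the PEEP benefit, and assume that the rest of the package lengthens ventilation:

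- by 10%: 0.75 × 1.10 = 0.825
- by 20%: 0.75 × 1.20 = 0.90
- by one third: 0.75 × 1.333 = 1.00

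The last case is a true null for the strategy alongside a real PEEP benefit. The lengthening figures are assumptions, not values from the protocol, and length of ventilation is a secondary outcome. They show only that the inference fails.

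**5. The test.** Study outcome specifies a one-sided Wilcoxon rank sum test at 0.05. A non-significant result is compatible with a benefit too small to detect, with no effect, and with an effect in the unfavourable direction. Even without the package, it would not show absence of effect.

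**The case against.** The strongest reply is that this is a strategy trial and says so. Study design and setting opens by comparing MBV with standard practice, Two-arm RCT sets out the package openly, and the Discussion describes a protocolised staircase manoeuvre combined with software. Elastance is measured at each PEEP step of a manoeuvre, and the algorithm cannot account for patient effort, so much of the recruitment and sedation is how the selection is made. Comparing such a method with usual care is legitimate. All of this stands, and it is why the design needs no change. It does not rescue a sentence that singles out the metrics, and the first RM_Max has a recruiting purpose beyond measurement.

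A second reply is mitigation. Under ABG recordings, samples taken around manoeuvres are left out of the primary analysis; sedation is recorded; SpO2 targets are common to both arms. This helps in part. The retained 0600 sample falls 12 hours after the routine PUMP window (0800–1800) closes, but the retained 1800 sample falls at its close and can still carry a recent recruitment effect.

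A reader might go further and infer that a positive result is uninterpretable too, or that control patients get no recruitment at all. The documents support neither. The stated reading of a difference concerns MBV against SPV, which is valid for the package. SPV patients may have an SRM with the same sedation instruction and rocuronium, so the imbalance is in scheduled exposure.

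**Conclusion.** The point holds for the null rule and for the framing of the aim. The two-arm contrast identifies the effect of the MBV strategy against usual care. The claim that no difference would show model-based metrics to be without effect is wrong on two counts: the metric is not isolated, and non-significance is not evidence of no effect. The second count holds even if the manoeuvres and sedation had no effect of their own.

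The aim in the abstract and the objective under Study design and setting are looser than the design supports, because they name PEEP selection without the rest of the package. The limitations in the Discussion mention that not all patients benefit from manoeuvres, that the manoeuvre is design specific and that control practice varies, but not the planned difference between arms in manoeuvres and sedation.

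The size can be given only as scheduled exposure: up to 42 staircases in 20 PUMP sessions and one double RM_Max, against none. No share of any effect can be assigned to a component from this design. The validity of the randomised comparison is not in question.

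**What to change.** 1. Under Study design and setting and under Study outcome, replace the null sentence. Suggested wording: a non-significant result will mean that a benefit of the MBV strategy over SPV was not demonstrated; it will be read with the effect estimate and its confidence interval, and not as evidence about the elastance metric alone. The sentence on a difference can stay.
2. In the abstract's Discussion paragraph and in the primary objective, word the aim as the effect of the MBV strategy, meaning protocolised manoeuvres with their sedation plus software-recommended PEEP, against standard practice.
3. In the Discussion, add the between-arm imbalance in scheduled manoeuvres and accompanying sedation to the limitations, and note that leaving out the blood gases around manoeuvres reduces its influence on the primary outcome only in part.

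Reporting set PEEP and manoeuvre counts by arm would help readers interpret the result. It is optional, and commonly left to the analysis plan.

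The cost is a few sentences and a narrower claim. Treatment, enrolment and sample size do not change.

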### ABG recordings

The primary outcome of this trial is the AUC of the P/F ratio. For this reason, mandatory daily ABG recordings are performed for up to 10 days after enrolment. ABGs are taken around 0600 hours and 1800 hours. The ABGs are also acquired within 60 min of any recruitment manoeuvre procedure and 30–60 min after the recruitment manoeuvre procedure. The added ABGs from RM procedures will be used in secondary analysis, but will be omitted during primary analysis to ensure the same number of data points per day for all patients.

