### Duration of the intervention

Patients randomised to the model-based ventilation (MBV) cohort will remain in the protocol up to 10 days. Thereafter, they will receive the same care as participants assigned to standard practice ventilation (SPV). However, if participants have been extubated, but then require intubation and re-ventilation at any time within 10 days of enrolment, they will return to the original assigned protocol (MBV or SPV). All patients will receive standard care beyond 10 days of enrolment, and their data, including ABG recordings, will continue to be collected for up to 28 days. This intervention schedule is shown in Fig. 1.

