### Sample size study

A Monte-Carlo simulation was performed to determine the sample size and determined that a minimum effective sample size of approximately 160 patients per arm is required to identify a 25% reduction in median LoMV, with 0.8 power, at a double-sided significance level of 5% [37].

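### The primary AUC of P/F accumulates over each patient's own ventilation time, so at equal oxygenation a shorter time on the ventilator scores worse

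*Protocol article*

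**What the plan says.** Two sections of the protocol article define the primary outcome. Study design and setting has "The primary outcome of this study is the area under the curve (AUC) of PaO2/FiO2 over the period of mechanical ventilation". Study outcome has "The trial will utilise a primary composite end point incorporating the AUC of the P/F ratio over the period of MV". Table 1 gives the metric as a difference in AUC, aggregated as "Comparisons of the of means of AUC". The abstract says only that the curve runs over time.

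The test is fixed as follows: "Test statistics will be calculated using the one-sided Wilcoxon rank sum test at alpha of 0.05". The same section says that a non-significant result leads to rejection of the intervention as a standard of care.

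On sampling, the ABG recordings section says "mandatory daily ABG recordings are performed for up to 10 days after enrolment", at about 0600 and 1800 hours. The extra gases around recruitment manoeuvres "will be omitted during primary analysis to ensure the same number of data points per day for all patients". Under Duration of the intervention, after day 10 "their data, including ABG recordings, will continue to be collected for up to 28 days".

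The Sample size study section gives about 160 patients per arm, "required to identify a 25% reduction in median LoMV", with power 0.8 and a two-sided 5% level.

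**The concern.** An area under a curve is average height times width. Here the width is each patient's own time on the ventilator, which is itself an outcome that the intervention is meant to change. The article equalises the number of gases per day but not the number of days. No section divides the area by its duration, sets a window common to all patients, or says how days after extubation or after death are scored.

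Two consequences follow. A patient liberated early scores lower than one with the same oxygenation who stays ventilated. Early death and early extubation both shorten the curve, so they move the score in the same direction. The planned test could therefore miss an intervention that improves oxygenation and shortens ventilation, and could favour one that only prolongs ventilation.

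**Working it through.** **The plan's own figure.** The 160 per arm concerns LoMV, not the AUC, and the article gives no LoMV distribution, so it cannot be reproduced from the text. It can be inverted. For log-normal LoMV, n per arm = 2(1.960 + 0.842)² × SD² / (ln 0.75)². With n = 160 and ln 0.75 = −0.288, the log-SD is 0.92. With the Wilcoxon efficiency factor 3/π it is 0.90. Log-SDs of 0.7 and 1.2 would need 98 and 287 per arm (Wilcoxon). A log-SD of 0.9 is therefore compatible with the plan's own sizing and is used below.

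**Arithmetic.** AUC = mean P/F × days ventilated.
- At an illustrative mean P/F of 180, 8 days gives 180 × 8 = 1440. With LoMV 25% shorter, 6 days gives 180 × 6 = 1080, which is 25% lower.
- To recover 1440 in 6 days, mean P/F must be 1440 / 6 = 240. That is 240 / 180 = 1/0.75 = 1.33 times as high, a 33% rise.

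**Simulation.** From the document: 160 per arm, 1:1 allocation, one-sided Wilcoxon at 0.05. Assumed: log-normal LoMV with log-SD 0.9 and control median 4, 6, 8 or 10 days; P/F log-SD 0.25, independent of LoMV; curve cut at 10 or 28 days. There were at least 2,000 trials per setting. With no difference between arms, rejection was about 5%, as it should be.

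| True effect of the intervention | AUC as written: test favours intervention | Time-averaged P/F: test favours intervention |
|---|---|---|
| P/F +10%, LoMV −25% | under 1% in seven of the eight settings; about 1.3% at median 10 days with a 10-day cut | about 95% |
| P/F equal, LoMV −25% | 0% | about 5% |
| P/F equal, LoMV +25% | about 43–67% | about 5% |

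**Sensitivity.**
- With P/F +20% and LoMV −25%, the AUC as written succeeds in about 0.2–9% of trials for medians of 4 to 8 days, and in about 22% at median 10 days with the 10-day cut.
- With P/F +10% and LoMV only 10% shorter, it succeeds in about 4–24%.
- If longer-ventilated patients have worse P/F (correlation −0.4, medians 4 and 7 days), the first row is at most 0.2% and the third is 66–75%.
- A 10-day cut softens the effect but does not remove it.

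The simulation gives each patient a single mean P/F, so the time average is free of duration by construction. Real P/F changes over the stay, so a real average would keep some dependence on the window. It would not scale in proportion to it.

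**The case against.** The strongest reply is that the article never says the AUC is unscaled. It speaks of a composite end point that incorporates the AUC, compares every intervention patient with every control patient, and is a condensed account whose analysis plan is not shown. That limits what can be said about intent. It does not remove the point: both definitions state the period of integration, and it is the patient's own. No further component is named, and the every-with-every comparison is what an ordinary rank sum test does. That a higher AUC counts as better is also implied, by the oxygenation rationale and the one-sided test, rather than stated.

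The sizes depend on assumed spreads, and the 25% is a detectable difference for sizing, not a forecast. This stands. The direction is arithmetic; the percentages are a range under assumptions.

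Three stronger readings do not hold:
- A reader might infer that the 10-day gas schedule contradicts an AUC over the whole ventilation period. Gases continue to be collected to day 28, so the cut-off is unstated, not contradictory.
- A reader might infer that the trial would declare harm. In the first scenario, an opposite-direction test would be significant in roughly 13–58% of trials depending on the assumptions, but no such test is planned. The planned result is a failure to show benefit.
- A reader might infer that the trial as a whole cannot answer its question. LoMV, ventilator-free days and mortality are separate outcomes, so prolonged ventilation would be visible there. The defect lies in the primary test.

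**Conclusion.** The point holds for the primary outcome as the article words it. At equal oxygenation the score falls in proportion to ventilated time, up to any cut-off. The LoMV reduction used for sizing lowers an uncapped AUC by 25% and needs a 33% rise in P/F to offset it. Under the assumptions above, the planned test has almost no chance of showing benefit when P/F is 10% higher and LoMV 25% shorter, and about a 43–67% chance of showing a false benefit when LoMV alone is 25% longer. Because a non-significant primary result is tied to rejecting the intervention as a standard of care, an effective intervention could be turned down on this ground. It should be corrected before recruitment.

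**What to change.** Define the primary outcome as time-averaged P/F: the AUC from the scheduled 0600 and 1800 gases divided by the time over which it is computed. State one maximum window, for example days 0–10, which matches both the mandatory gas schedule and the intervention period. Use identical wording in the abstract, Study design and setting, Table 1, ABG recordings and Study outcome.

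The cost is wording only. No new data are needed, and the Trial status section says recruitment has not begun. The remaining limitation is that an average over ventilated time gives no credit for early liberation and no penalty for death, so ventilator-free days and mortality should be reported directly beside it.

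A ranked composite with death worst and liberation best would address that limitation. It would change the question from oxygenation towards survival and liberation, was not simulated here, and would need its own power calculation. It is an option, not a requirement.
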